##### Histopathological examination and further allocation

3.1.3.1

Biopsy specimens (resected polyps and samples of normal colonic and ileil mucosa) will be fixed in 10% buffer formalin 24-48 hours at room temperature, processed and embedded in paraffin (FFPE). The FFPE sample sections will be cut at 3 μm thickness and mounted on positively charged slides. All slides will be stained with hemotoxylin-eosyn (HE) for the accurate evaluation of polyps and healthy colon histology.

Patients with non-adenomatous mucosal and sessile serrated lesions will be eliminated from the study. Only patients with histopathologically confirmed colorectal adenoma (small/large), carcinoma *in situ* and adenocarcinoma are being selected for further examination and become study participants. These patients will be divided into 4 exposure groups according to the CR neoplasia size and the dysplasia level, and 4 self-control groups (patient serves as his own control), and the general control group V as an overall healthy patients’ control (**Table 2**). Patients with macroscopically normal but histologically confirmed adenomatous or non-adenomatous mucosal lesions in control-site biopsies will not be enrolled in further examination and so will be eliminated from the study.

**Table 2 T2:** Histology- and size-based allocation of participants.

Exposure	Control
Group I (N=10): endoscopically removed and histopathologically confirmed up to 1 cm sized (low-grade dysplasia) tubular/tubulovillous/villous adenoma;	Control group 1: biopsy samples from group I patients’ terminal ileum, right- and left-sided healthy colon;
Group II (N=10): endoscopically removed and histopathologically confirmed 1 cm or greater (low- or high-grade dysplasia) tubular/tubulovillous/villous adenoma;	Control group 2: biopsy samples from group II patients’ terminal ileum, right-and left-sided healthy colon;
Group III (N=10): endoscopically removed/sampled and histopathologically confirmed Ca *in situ* (high-grade dysplasia);	Control group 3: biopsy samples from group III patients’ terminal ileum, right- and left-sided healthy colon;
Group IV (N=10): endoscopically sampled and histopathologically confirmed invasive adenocarcinoma;	Control group 4: biopsy samples from group IV patients’ terminal ileum, right- and left-sided healthy colon;
Control group V (N=10): patients, without any polypoid lesions found during colonoscopy (mucosal biopsies from their terminal ileum, right- and left-sided healthy colon).	

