**Methods and analyses:**

This study aims to prospectively recruit 40 patients (10 per group) with confirmed colorectal dysplasia undergoing endoscopic polypectomy, endoscopic mucosal resection for colorectal small (≤1cm), and large (>1cm) adenoma or carcinoma in situ, or biopsy and subsequent colon resection for invasive colorectal cancer, and 10 healthy patients undergoing screening colonoscopy. Stool samples will be collected prior to bowel preparation for the analysis of fecal (luminal) microbiota composition. Biopsy specimens will be taken from the terminal ileum, right colon, left colon, and a pathological lesion in the colon (if present) to assess mucosa-associated microbiota composition and intestinal immunity response. DNA will be extracted from all samples and sequenced using the Illumina MiSeq platform. Unifrac and Bray-Curtis methods will be used to assess microbial diversity. The intestinal immune system response will be examined using digital image analysis where primarily immunohistochemistry procedures for CD3, CD8, CD20 and CD68 immune cell markers will be performed. Thereafter, the count, density and distribution of immunocompetent cells in epithelial and stromal tissue compartments will be evaluated using AI-based platform. The interaction between the microbial shifts and intestinal immune system response in adenoma-carcinoma sequence and the healthy patients will be examined. In addition, fecal samples will be explored for gut microbiota’s composition, comparing fecal- and tissue-derived bacterial patterns in healthy gut and along the adenoma-carcinoma sequence.

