##### Inclusion criteria for exposure groups

2.2.1.1

Patients with histologically confirmed dysplastic colorectal lesion: early and advanced-adenoma, carcinoma *in situ* or adenocarcinoma. Advanced adenomas are defined as those with high-grade dysplasia, villous or tubulovillous histology, or a diameter ≥1 cm;Adult patients (≥18 years);Written informed consent.

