##### Exclusion criteria

2.2.1.3

Patients under the age of 18 years;Confirmed serrated (sessile serrated (SSA), traditional serrated adenomas (TSA)) or hyperplastic polyps or non-polypoid lesions;Signs of colorectal tumor obturating the lumen of the bowel which would limit complete colonoscopy;Suffer from other gastrointestinal tumors;Pregnancy;Previous colon resection;History of surgery disrupting gastrointestinal tract integrity;History of inflammatory bowel disease (ulcerative, Crohn’s, radiation-induced, or infectious colitis or other previous chronic inflammatory illnesses);Familial adenomatous polyposis (FAP) or other hereditary colon syndromes;Clinically significant immunodeficiency;Evidence of infection;During the last year patient had:- suffered from *Cl. difficile* colitis or was a carrier of *Cl. difficile*; suffered from salmonellosis or other gastrointestinal infection;- a long-term (> 6 months) use or recently completed therapeutic antibiotic course within the last month;- corticosteroid and/or immunosuppressant therapy;- received chemo- or radiation therapy in the abdomen and/or pelvis chemotherapy;- regular use (> 3 months) of pre-/pro-/(sin)biotics and/or statins;- a long-term (> 6 months) use of proton pump inhibitors;Patients who cannot undergo colonoscopy on time and cannot cooperate fully.

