## Interventions

3

Adult patients who have been referred to a screening/diagnostic/therapeutic colonoscopy and during procedure will be diagnosed with CR polyps, as a common practice of colorectal dysplasia management will undergo (if no contraindications):

- endoscopic polypectomy, in case of simple CR adenoma;- endoscopic mucosal resection (EMR) or endoscopic submucosal dissection (ESD), in case of advanced, flat/over the fold/right-sided colon CR adenomas or Ca in situ;- TEM (transanal endoscopic microsurgery) in case of large rectal adenomas or Ca in situ;- sampling and subsequent colon resection in case of colorectal cancer or unresectable colon polyps.

During the same procedure seven mucosal biopsy specimens from each region (macroscopically healthy right- and left-sided colon, terminal ileum, and pathologic lesion, if present) will be obtained. In order to prevent possible cross-contamination from other parts of the bowel (especially important in tissue specimens being sampled for microbiota compositional analysis), sterile biopsy forceps will be used for each region and each biopsy location. Resected polyps and mucosal biopsy specimens from unaffected bowel regions will be sent to histological, IHC, DNA sequencing examination and further genetic testing for specific oncogenic mutations (in the next trial). In terms of the study, no further visits to the hospital will be required.

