### Limitations of the study

5.2

The single-centre type of this study could be a limit, potentially exposing to recruitment biases. The efforts to avoid selection bias could also be hindered by the fact that sessile serrated lesions as the alternative pathway of colorectal carcinogenesis are not being examined. The study could also be hampered due to the restricted examination of mainly bacterial microbiota composition. The sample size of about 50 participants nevertheless responds to 190 sampling sites, 570 tissue specimens and 50 stool samples being examined for microbiota and local immunity structures, therefore, is not considered small, especially in the light of human gut microbiota studies (63). Due to expected lower incidence of Ca *in situ* lesions in the population, the study has a risk of being limited by the lack of samples in III exposure group. However, in that case the risk could be mitigated by relocating exposure groups and representing adenoma-carcinoma sequence in the form of subsequent dysplasia examination from small (early) and large (advanced) adenomas as initial stages and invasive carcinomas (Ca *in situ* and adenocarcinoma) as the progression of the disease.

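### The rules that assign lesions to exposure groups conflict: some adenomas fit two groups or none, and carcinoma in situ carries three meanings

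*Protocol article*

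**What the plan says.** Section 3.1.3.1 allocates patients to four exposure groups by lesion size and dysplasia grade. In Table 2, Group I is "up to 1 cm sized (low-grade dysplasia) tubular/tubulovillous/villous adenoma", Group II is "Group II (N=10): endoscopically removed and histopathologically confirmed 1 cm or greater (low- or high-grade dysplasia) tubular/tubulovillous/villous adenoma", and Group III is "endoscopically removed/sampled and histopathologically confirmed Ca *in situ* (high-grade dysplasia"), with no size limit.

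Other sections define the same stages differently:

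- Section 2.2.1.1: "Advanced adenomas are defined as those with high-grade dysplasia, villous or tubulovillous histology, or a diameter ≥1 cm".
- Abstract, Methods and analyses: "small (≤1cm), and large (>1cm) adenoma or carcinoma in situ".
- Section 1.2: two tasks divide early from advanced at under and over 1 cm; the last task uses under 1 cm and at least 1 cm.
- Figure 1 legend: carcinoma in situ is carcinoma within an adenoma, or intramucosal carcinoma.
- Section 5.2: if Group III is short, the groups may be rearranged, with "invasive carcinomas (Ca *in situ* and adenocarcinoma) as the progression of the disease".
- Section 5.3: carcinoma in situ is counted with adenoma as precancerous.

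**The concern.** Section 3.1 makes the comparison of dysplasia steps with healthy controls part of the primary outcome. Section 5.1 predicts differences between high- and low-grade dysplasia and between lesions of at least 1 cm and smaller ones. These are the boundaries on which the rules disagree. If two competent readers can place the same lesion in different groups, the exposure is not reproducible. A lesion that meets two definitions could also be placed wherever patients are needed, and section 5.2 already expects Group III to be hard to fill.

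The fallback raises a further problem. Section 5.1 reads microbial patterns around premalignant lesions as pointing to a primary role, and patterns around carcinoma as secondary. Pooling carcinoma in situ with adenocarcinoma moves lesions that section 5.3 calls precancerous to the carcinoma side of that contrast.

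**Working it through.** The plan's own totals reproduce and are not disputed: 5 groups × 10 = 50 patients; 40 × 4 + 10 × 3 = 190 biopsy locations. The check is on the rules. Take every adenoma type formed by size (under, exactly, over 1 cm), grade (low, high) and histology (tubular; tubulovillous or villous): 3 × 2 × 2 = 12 types. Apply Table 2 under two readings of Group III. Reading A takes carcinoma in situ to equal high-grade dysplasia, as in Table 2's bracket. Reading B takes it to be intramucosal carcinoma, as in the Figure 1 legend.

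| Size | Grade | Histology (types) | Table 2, A | Table 2, B | 2.2.1.1 | Abstract |
|---|---|---|---|---|---|---|
| <1 cm | low | tubular (1) | I | I | not advanced | small |
| <1 cm | low | tubulovillous/villous (1) | I | I | advanced | small |
| <1 cm | high | either (2) | III | none | advanced | small |
| 1 cm | low | either (2) | I and II | I and II | advanced | small |
| 1 cm | high | either (2) | II and III | II | advanced | small |
| >1 cm | low | either (2) | II | II | advanced | large |
| >1 cm | high | either (2) | II and III | II | advanced | large |

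- Reading A: 2 + 2 + 2 = 6 of 12 types fit two groups in Table 2; none lacks a group.
- Reading B: 2 types fit two groups and 2 fit none, so 4 of 12 lack a single group.
- Under both readings, 1 further type (small, low-grade, tubulovillous or villous) is Group I in Table 2 but advanced in section 2.2.1.1.
- Only 1 + 2 = 3 types are placed alike by every rule under both readings. The other 9 meet a conflict under at least one reading.

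These are counts of lesion types, not shares of patients. The article does not say how common each type is.

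The size cut: a lesion of exactly 1 cm is small in the abstract, in neither class in two tasks of section 1.2, advanced in the last task and in section 2.2.1.1, and in both Group I and Group II in Table 2 if low-grade.

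Group size: with 10 per group, one lesion is 1/10 = 10% and three are 30%. At the upper recruitment figure of 15, three are 3/15 = 20%.

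**The case against.** The overlap of Groups II and III is not certain. Each bracket in Groups I to III gives a grade, so the one in Group III can be read as describing carcinoma in situ rather than defining it. With the Figure 1 meaning, a large high-grade adenoma belongs to Group II alone. That stands, but the same reading leaves the small high-grade adenoma without a group. The two faults are alternatives, and one of them arises either way.

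The villous conflict may be called terminology: section 2.2.1.1 decides eligibility, and such lesions are eligible whatever they are called. That is fair, but section 1.2 also uses advanced as the name of a stage, so results for that stage would describe different lesions depending on the section followed. The 1 cm point affects only a boundary, and most passages favour at least 1 cm for the upper class; Table 2 still overlaps there.

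Allocation after histology is the design and no loophole: Table 1 places it before sequencing and image analysis. This protects lesions with an unambiguous group. The fallback has no stated timing.

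A reader might infer that the exclusion "or hyperplastic polyps or non-polypoid lesions" removes flat adenomas, which section 3 lists for treatment ("in case of advanced, flat/over the fold/right-sided colon CR adenomas or Ca in situ"), and even non-polypoid cancers from Group IV. The article defines neither flat nor non-polypoid, and section 3 describes usual care. Adenocarcinoma is expressly included in section 2.2.1.1 and Table 2. The flat-adenoma question needs clarifying; the Group IV inference is not supported.

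**Conclusion.** The allocation rules conflict, and this is stated text rather than detail left to another document. Four faults hold: the overlap at exactly 1 cm with an inconsistent cut; three meanings of carcinoma in situ, which produce either a II/III overlap or a gap for small high-grade adenomas; two definitions of advanced adenoma; and a fallback that calls carcinoma in situ invasive.

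A few ambiguous lesions can materially change a group of 10. A reader might want to turn this into a loss of power. The documents do not allow it: they give no effect size, no standard deviation and no frequency of ambiguous lesions, and the planned analyses are rank-based and multivariate. Nor does the fallback abolish the contrast in section 5.1. It is a contingency under which small adenoma, large adenoma and carcinoma remain separate; it weakens the premalignant-versus-carcinoma comparison. Not every primary comparison is affected equally, since section 3.1 also compares tumour localizations and section 3.1.3.1 adds within-patient controls.

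**What to change.** Reconcile the abstract, section 1.2, the Figure 1 legend, section 2.2.1.1, Table 2 and section 5.2 to one hierarchical, mutually exclusive rule:

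- one size cut, under 1 cm against at least 1 cm, as already used in the last task of section 1.2, in section 2.2.1.1 and in section 5.1;
- one definition of carcinoma in situ, chosen by the investigators with their pathologists;
- one definition of advanced adenoma, used for both eligibility and Table 2;
- an explicit group for high-grade adenomas under 1 cm.

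Correct the invasive label in section 5.2. Fix how groups would be pooled if Group III is short, in line with the chosen definition and before group results are seen. Which lesions to pool is a pathology judgement that the article does not settle. As a minor point, state whether flat adenomas fall under the non-polypoid exclusion.

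Apply the rule to existing histology reports, blind to microbiota and immune results, and document the change as section 2.1.2 requires. No new samples or procedures are needed. The cost is that some patients already allocated may change group, and a narrower definition of carcinoma in situ would make Group III, already expected to be scarce, harder to fill.

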##### Immunohistochemistry and AI-based digital image analysis of intestinal mucosal tissue

3.1.3.2

Immunohistochemical staining will be performed using the Roche Ventana BenchMark ULTRA (Ventana Medical Systems, USA) automated slide stainer. Monoclonal antibodies against B lymphocytes (CD20), T lymphocytes (CD3), cytotoxic T-lymphocytes (CD8) and macrophages (CD68) will be used.

HE, CD3, CD8, CD20, CD68 slides will be scanned using a ScanScope XT Slide Scanner (Leica Aperio Technologies, CA, USA) or an Aperio 18 AT2 Slide Scanner (Leica Microsystems, Wetzlar, Germany) with 20x magnification (0.5 μm resolution). Digitized whole-slide images will be archived in a pathology image database ImageScope (version 11.1.2.752, Leica Biosystems, Chicago, USA), then transferred to a DIA platform HALOTM (version 2.2.1870, Indica Labs, New Mexico, USA).

The intestinal immune system response will be examined using digital pathology image analytics. Primarily, IHC procedures for the visualization of the immune cell markers (CD3, CD8, CD20 and CD68) will be developed and optimized to fit the requirements of DIA. Multiplex IHC will be used to enhance the analysis where both cell populations with specific biological properties and their spatial interactions at the cellular and regional level in tissue microenvironment are included. Then, digital image processing procedures will be established for the robust immune cell infiltrate quantification and analysis of spatial distribution patterns in the intestinal tissues. Analysis of cell population (CD3, CD8, CD20, CD68) will be completed by employing HALO Multiplex IHC module. The methodology that combines DIA, artificial intelligence tools and based on explicit rules will be employed.

The analysis workflow follows: 1) the training of artificial intelligence-based HALO AI classifier to segment the intestinal tissues into classes (stroma, non- malignant epithelium, malignant epithelium etc.); 2) the detection and quantification of immune cell counts/densities in epithelial and stromal compartments. Finally, immune cell population distribution and interaction patterns will be correlated to the composition of the gut microbiota and pathology features. The findings will enable us to generate informative combinatorial models to achieve more precise prediction of CRC development.

##### 16S rRNA gene sequencing for microbiota examination from tissue and fecal samples

3.1.3.3

Tissue samples including lesion (or para-lesion in case of small (<1cm) adenoma), right- and left-sided normal appearing colon and terminal ileum mucosa will be obtained from the participants during colonoscopy or surgery. Intestinal mucosal specimens will be frozen and stored in the − 80°C refrigerator for later use. Similarly, fecal samples of patients will be frozen and stored at − 80°C immediately after they have been received in the study centre.

The total DNA of frozen samples will be extracted by mechanical and enzymatical cell lysis. DNA integrity and concentration will be assessed by the NanoDrop ND-1000 spectrophotometer (Thermo, USA). The bacterial 16S rRNA V3–V4 regions will be amplified via polymerase chain reaction (PCR), and high-throughput sequencing will be conducted on an Illumina platform. Raw reads will undergo denoising and preprocessing utilizing the tools provided by the Quantitative Insights Into Microbial Ecology 2 (QIIME2) software pipeline platform using default settings, unless specified otherwise. The DADA2 workflow will be utilized to construct the amplicon sequence variants (ASV) table, and sequences will be aligned to build a phylogenetic tree. Low abundant sequences will be excluded from analysis. Taxonomic analysis will be conducted with a Naïve Bayes Classifier, leveraging on the SILVA 138.1 database.

## Data and statistical analysis

4

The questionnaires and other measured data during the visit will be collected on paper and then transcribed to a secure electronic version on a locked office computer. The paper version of the data will be locked in a bookcase. Only the investigators running the study will have access to the final study dataset.

The obtained data will be analyzed by the SPSS software V26.0 (IBM, USA). The count, density, and distribution of immunocompetent cells (CD3, CD8, CD20, CD68) in epithelial and stromal compartments of adenoma, Ca in situ, CRC and the healthy controls will be performed. Here, continuous data with normal distribution will be expressed as mean ± standard deviation (SD), while data that is not normally distributed as median and range. Categorical data (especially from the questionnaires) will be expressed as the number of cases (n) and percentage (%). Kruskal-Wallis Test followed by Dunn’s Test will be employed for multiple pairwise comparisons of differences between two and more groups.

As for statistical analysis of microbial data, relative abundances, alpha and beta diversity will be performed. Principal Coordinates Analysis (PCoA) will be executed after calculating Bray-Curtis dissimilarity and UniFrac distances between samples. Beta diversity analyses will involve the application of Hellinger transformation to account for the compositional nature of microbiome data. Cluster analysis will be performed using Analysis of Similarities (ANOSIM) to assess the significant differences in microbial community composition between sample groups. Redundancy analysis will be used to identify factors that influence the structure of the microbiome. Alpha diversity will be calculated through the Shannon index, Simpson index, and Chao1 metrics after appropriate rarefaction. For the identification of differences in specific taxa between groups, ANCOM and LEfSe analysis will be conducted.

The correlation between the gut bacterial composition and intestinal immune system response in adenoma-carcinoma sequence, and the healthy patients will be examined. Furthermore, fecal samples will be explored for gut microbiota alterations, comparing fecal- and tissue-derived bacterial compositions in healthy gut and along the steps of conventional colorectal carcinogenesis. The results will be regarded as statistically significant if p values < 0.05. In case of a relevant number of missing values, multiple imputation or pattern mixture models will be used.

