### Data collection and management

3.1

Assessment of participants will be conducted at the pre-procedure (-t1), procedure (0) and post-procedure (t1-t4) timepoints. The detailed schedule of assessments is depicted in **Table 1**. The primary outcomes will be the differences in the microbiota composition and immune infiltration in different localizations of the tumor and different steps of mucosa dysplastic lesions compared to healthy controls. The secondary outcomes include correlation analysis of gut microbial diversity, intestinal immunity variables and the grade of colorectal dysplasia assessed for the study.

**Table 1 T1:** Study schedule of enrolment, interventions, and assessments.

	STUDY PERIOD						
	Enrolment	Allocation	Examination and analysis period				Close-out
TIMEPOINT	*-t_1_ *	0	*t_1_ *	*t_2_ *	*t_3_ *	*t_4_ *	*t_x_ *
ENROLMENT:							
Eligibility screen	X						
Informed consent + filling the questionnaire	X						
Allocation		X					
INTERVENTIONS:							
Collection of fecal samples	X	X					
Colonoscopy + endoscopic polypectomy (or biopsy) and normal gut tissue sampling or right hemicolectomy and gut tissue sampling	X		X				
ASSESSMENTS AND DATA ANALYSIS:							
Pathologic investigations: HE and IHC	X	X	X				
16S rRNA gut tissue- and fecal-derived microbiota sequencing			X	X	X	X	
AI-based digital image analysis			X	X	X	X	
Qualitative data analysis based on the questionnaires		X	X				
Data analysis on intestinal immune infiltration variables: count, density, and distribution of CD3, CD8, CD20, CD68 cells in epithelial and stromal compartments				X	X	X	X
Data analysis on gut microbiota compositional changes in tissue and stool samples: relative abundance, α- and β-diversity, etc.				X	X	X	X
Correlation analysis of gut microbiota and immune response variables in different site of the colon along the adenoma-carcinoma sequence						X	X

X, mark the appropriate period for the enrollment, interventions and other activities during the project

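### Immune-cell count is compared between groups beside density with no reference area, so unequal analysed tissue area can appear as a group difference

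*Protocol article*

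**What the plan says.** Section 4 lists the immune measures as "The count, density, and distribution of immunocompetent cells (CD3, CD8, CD20, CD68) in epithelial and stromal compartments", and says that the Kruskal-Wallis test followed by Dunn's test "will be employed for multiple pairwise comparisons of differences between two and more groups". The same trio of measures appears in the tasks of Section 1.2 and in Table 1. Immune infiltration belongs to the primary outcome: "The primary outcomes will be the differences in the microbiota composition and immune infiltration in different localizations of the tumor" (Section 3.1).

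Section 3.1.3.2 digitises whole slides, segments the tissue, and then plans "the detection and quantification of immune cell counts/densities in epithelial and stromal compartments". It states no fixed field, reference area or normalising rule for the count.

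On the tissue itself, Section 3 says "Resected polyps and mucosal biopsy specimens from unaffected bowel regions will be sent to histological, IHC, DNA sequencing examination", and Section 3.1.3.1 says "Biopsy specimens (resected polyps and samples of normal colonic and ileil mucosa) will be fixed in 10% buffer formalin". Table 2 describes the lesion material by group:

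- Group I: "endoscopically removed and histopathologically confirmed up to 1 cm sized".
- Group II: "endoscopically removed and histopathologically confirmed 1 cm or greater (low- or high-grade dysplasia".
- Group III: removed or sampled.
- Group IV: sampled.
- Group V: mucosal biopsies only.

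Section 3 also takes seven mucosal biopsies from every region, the lesion included. Section 3.1.2 repeats the forceps sampling and places it beside the lesion for adenomas under 1 cm.

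**The concern.** A cell count can be compared between specimens only if the same amount of tissue was examined. Whole-slide quantification counts whatever lies on the section, so the expected count is density multiplied by analysed area. Segmenting into epithelium and stroma does not change this. Segmentation defines the compartment, and only division by its area normalises the count.

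If the resected polyp is what is analysed, the area on the slide is linked to the group definition. Groups I and II are separated by lesion size, and Group V has no lesion specimen. A difference in count could then arise with no difference in infiltration. Section 5.1 expects a stronger immune response in polyps of 1 cm or more than in smaller ones. In that contrast an area effect on count would look like confirmation.

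**Working it through.** **1. The plan's own specimen figures.** Section 2.2.4 gives 190 locations, 570 tissue samples and 2280 stained specimens. These reproduce: 40 × 4 + 10 × 3 = 190; 190 × 3 = 570; 570 × 4 = 2280. The totals imply the same three samples at every location, lesion or normal. That fits uniform forceps sampling.

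**2. The two readings side by side.**

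- *Resected polyp analysed* (Sections 3 and 3.1.3.1, Table 2): lesion tissue is a whole removed polyp in Groups I and II, mixed in III, sampled in IV and absent in V. Area differs by group, and between I and II by definition.
- *Forceps biopsies analysed* (Sections 2.2.4, 3 and 3.1.2): fragments are nominally alike, so lesion size does not enter directly. Group I is still represented by mucosa beside the lesion, whereas larger lesions are sampled themselves. The share of epithelium and stroma in a section may therefore still differ. No figure in the article measures this.

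The article does not choose between the two readings.

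**3. Size of the effect if areas differ.** The article gives no areas and no variability, so all of the following are assumptions, shown over a range.

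- Five groups of 10 (group size from Section 2.2.4), one value per patient, and identical true density in every group.
- Count = density × area, both lognormal, with SD of the log = √ln(1 + CV²).
- Density CV 0.3, 0.5 or 0.8; within-group area CV 0.3 or 0.5.
- Relative areas: I = 1, II = r, III = √r, IV = 1, V = 1.
- 2000 simulated trials per setting, Kruskal-Wallis at 0.05.

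The width of the ranges follows from the CVs. At r = 2 the shift of Group II on the log scale is ln 2 = 0.693.

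- Least variable case (both CVs 0.3): SD of log count = √(0.086 + 0.086) = 0.415, so the shift is 0.693 / 0.415 = 1.67 SD.
- Most variable case (CVs 0.8 and 0.5): SD = √(0.495 + 0.223) = 0.847, so the shift is 0.693 / 0.847 = 0.82 SD.

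| Area ratio r | False rejection, count | False rejection, density |
|---|---|---|
| 1 | 3.6–4.4% | 3.8–5.1% |
| 1.5 | 12.6–47.8% | 3.6–4.9% |
| 2 | 33.6–94.7% | 4.2–5.2% |
| 3 | 74.9–100% | 3.0–5.3% |
| 4 | 94.1–100% | 3.7–5.0% |
| 9 | 100% | 4.2–4.8% |

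Each range spans the six CV combinations. At r = 1 count behaves correctly, so the excess is due to area alone. For Group II against Group V on count, a Mann-Whitney test (standing in for the Dunn comparison) falsely rejects in 36.2–90.7% of trials at r = 2.

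**The case against.** The strongest reply is that the area-normalised measure is already planned. Density appears beside count wherever count is listed, within segmented compartments. A reader might infer that the whole immune half of the primary outcome is compromised. The article does not support that, because only the count is exposed.

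A second reply is that nothing in the article calls the count an unnormalised total, and that regions of interest are detail an article may leave to a fuller document. This stands in part. However, density is listed separately, so count cannot simply be read as count per area, and the article does fix it as a compared measure.

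A third reply is that uniform forceps sampling may remove most of the contrast. This stands as a possibility, and the specimen totals favour it. It is why the bias can arise but cannot be called certain.

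Three further inferences go too far:

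- *That counts would rise through the stages.* Table 2 has Group IV sampled and Group II removed, so count could be highest in Group II and fall towards cancer. That runs against the cancer-versus-adenoma expectation in Section 5.1.
- *That the distortion is many-fold.* Treating sections as solid discs of 8 mm and 20 mm gives (20/8)² = 6.25. If area grows with length, as it may in flat lesions, the ratio is 20/8 = 2.5. Both diameters are assumed.
- *That lesion counts carry the artefact into the microbiota correlations.* Section 1.2 ties count to correlation only for normal bowel, where all samples are mucosal biopsies. Section 3.1.3.2 speaks of distribution and interaction patterns, and Table 1 of immune variables in general.

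**Conclusion.** The point holds in limited form. Count is a compared measure with no stated reference area, specimen type and lesion size are tied to group in Table 2, and the article leaves open which tissue is analysed. Where analysed tissue or compartment area differs between groups, the count comparison can reject at equal infiltration. Density is unaffected, staying at 3–5% at every ratio examined.

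The size depends on areas that the article does not give. A 1.5-fold ratio already inflates false rejection well above 5%, and a threefold ratio makes it the usual result. If areas are in fact equal, there is no inflation. All area ratios, their pattern across groups and the CVs are assumptions.

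**What to change.** In Section 1.2, Table 1 and Section 4, make density per mm² of classified compartment (epithelium and stroma separately) the immune measure in place of count, both for comparisons between groups and for the microbiota correlations. Report count and analysed area descriptively only. In Section 3.1.3.2, add one sentence for each group stating whether the resected polyp or the forceps biopsy enters image analysis, and reconcile it with Section 3, Section 3.1.2 and Table 2.

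The cost is one fewer compared measure and slight rewording. Compartment areas are already needed to compute density, so no extra laboratory or imaging work follows.
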